### Interventions

#### Information package

The intervention consisted of an innovative information package, posted directly to participants. The package clearly details the evidence-based management of acute back pain, based on recommendations from the UK evidence-based and evidence-linked multi-disciplinary primary care [21] and occupational [22] LBP guidelines. We originally considered producing our own information package. However, when designing the study we identified an existing, high quality, package that met our needs. This package was originally developed as part of an ongoing national, multi-intervention educational campaign in Scotland led by the Health Education Board of Scotland and the Health and Safety Executive, entitled 'Working Backs Scotland' (WBS) [15]. We used exactly the same package as the WBS package with an additional covering letter, which explained the origins of the package. We did not have sufficient resources to produce a new version of the pack to the same quality, in order to remove its Scottish origins. Since the issues in the management of LBP are likely to be similar in all parts of the UK, this should not affect the appropriateness of the package for our current purpose.

The novel approach taken by the WBS initiative was to produce a comprehensive and cohesive information package, suitable for multiple stakeholders (summarised in Table 2), as part of a national initiative similar to a high-profile and largely successful Australian study [9,10,88].

**Table 2 T2:** Components of the 'Working Backs Scotland' information package

**Targeted stakeholder**	**Component of package**
Patients	The Back Book (1st edition)
	Health & Safety Executive: Back in Work booklet
	Contextualised A4 sheet with recommendations
	Poster with recommendations for patients
	
All providers	Introduction letter from Working Backs Scotland
	
***Therapy Providers***	Contextualised A4 sheet with recommendations
	Royal College of General Practitioners: A4 guideline summary pamphlet
	Yellow Flags guideline summary
	
***General Practitioners***	Contextualised A4 sheet with recommendations
	Royal College of General Practitioners: A4 guideline summary pamphlet
	Yellow Flags guideline summary
	
***Pharmacists***	Contextualised A4 sheet with recommendations
	
***Employers***	Contextualised A4 sheet with recommendations
	Health & Safety Executive: Back in Work booklet

In order to maximise the likely success of the package, the contents were deliberately designed to target previously identified contextual 'barriers' to behaviour change. One suggested strategy for increasing the uptake of guideline recommendations has been local adaptation, in order to provide a sense of relevance and local 'ownership' of the recommendations [54,89,90]. However, there is some evidence that local adaptation of national guidelines has no effect on practitioner behaviour [91], suggesting that relevance and ownership should be provided in some other way. One alternative for providing these has been the production of unidisciplinary guidelines. An example of this has been the recent formation of physiotherapy guidelines in the Netherlands [13], an equivalent of which is also currently under development in the UK [92]. Unidisciplinary guidelines have the further advantage of being able to provide best practice recommendations on technical areas of clinical practice that have little relevance outside a particular healthcare professional group.

In the WBS package, an attempt has been made to simultaneously provide relevance for all stakeholder groups by supplying each with an individual, tailored A4 recommendation sheet, every sheet being consistent with the others [87]. Each A4 sheet includes only those recommendations most likely to be relevant to that particular group. This allows every stakeholder to see the consistent messages provided by the recommendations, with the aim of reinforcing these messages. Importantly, the specific behaviours targeted for all stakeholder groups are kept to a minimum [84] and focus predominantly upon LBP patients staying active, avoiding bed-rest, and staying at or returning to work. Intended specifically for the healthcare practitioners is a copy of the brief summary A4 pamphlet version of the RCGP guidelines [21], and an A4 summary sheet explaining the concept of psychosocial 'Yellow Flags' [93]. The package also includes a copy of the patient-orientated advice booklet, the first edition of 'The Back Book' [94], which has been formally tested by Burton et al [95], and a leaflet designed for employers and workers, 'Back in Work' [96], the messages of which are consistent with the guidelines.

Much like the principal recommendations of the original sources on which the WBS package was based [21-23], the wording of the recommendations on each contextualised A4 sheet are clearly written in the form of behavioural instructions; an important attribute in any intervention designed to change practitioner behaviour [97,98]. Credibility of the package is reinforced by several declarations that the contents of the package are based on the best international research evidence [97]. Furthermore, the commissioning body was expected to be well respected by all stakeholders ([name], personal communication). The issue of perceived ownership of the material [99] was addressed through considerable effort in enlisting and displaying the support of a wide range of local and national professional groups and societies (22 in total). These groups, including bodies representing the chiropractic, osteopathy and physiotherapy professions, endorsed both the initiative and the information package.

#### Control arm

Participants in the control arm were sent the standard brief description of the study with the baseline questionnaire, but were sent no further information prior to the six-months post-intervention follow-up questionnaire. Therefore, they received nothing other than they would during usual clinical practice. Of course no control could, nor should, have been exerted over other sources of information available to either arm of the trial. Being a pragmatic RCT with a large sample size, any other influences on clinical practice are likely to have been equal for each arm.

### Questionnaire development

The choice of outcome measures was guided by the findings from previous qualitative studies [41,44]. Permission to use previously published material was gained from the original authors of each outcome measure. The contents of the baseline and sixmonths post-intervention follow-up questionnaires are summarised in Table 3. The two most important outcomes measured in the study were (1) reported clinical behaviour (primary outcome), and (2) practitioners' attitudes and beliefs. Each outcome measure was slightly modified from the original version for the purposes of this study. A description and justification for each modification is given below.

**Table 3 T3:** Information collected in the self-completed questionnaires

**Information**	**Measure**	**Original authors**	**Items**	**Baseline**	**6 months**
Demographic details	Age Professional group Years qualified NHS/Private Back pain workload Personal history of back pain	-	-	Yes	No
Reported behaviour relating to a patient vignette with non-specific acute low back pain and no 'red flags'.	Questions relating to a low back pain patient vignette (modified from original studies)	Modified from: Bombardier et al 1995 [105] Rainville et al 2000 [109] Buchbinder et al 2001 [10] Bishop & Foster 2005 [49]	3	Yes	Yes
Practitioner beliefs concerning the way that low back pain is likely to affect function	Modified Health Care Providers Pain and Impairment Relationship scale (HC-PAIRS)	Modified from: Rainville et al 1995 [110] Houben et al 2004 [46]	13	Yes	Yes
Practitioner self- confidence in managing patients with low back pain	Practitioner self-confidence scale	Modified from: Bush et al 1993 [117] Smucker et al 1998 [118]	4	Yes	Yes
Practitioner attitudes towards the use of research and evidence in practice	Practitioners connections with research Authority of information sources to influence practice	Modified from: Connolly et al 2001 [119]	12	Yes	Yes

### Outcome measure 1: Reported behaviour

The primary outcome measure was a measure of reported clinical practice behaviour, captured using questions related to a single vignette of a patient with non-specific acute LBP and no 'red flags' for possible serious spinal pathology (Figure 2).

**Figure 2 F2:**
[figure not shown]
Patient vignette with non-specific acute low back pain and no 'red flags'.

Vignettes are hypothetical clinical presentations of patients intended to elicit from practitioners an underlying practice pattern or 'medical signature' [100]. Research has been conducted on the discordance between what physicians report they would do in response to a patient vignette and what they actually do in practice. Some investigators have raised concern to the value and validity of vignettes as an outcome measure in assessing practitioner behaviour [100-103]. Specifically, critics have argued that practitioner responses to vignette are likely to report what they perceive should be done rather than what they would actually do. However, a large, prospective study [104] has shown that vignettes are not only reliable, stable and valid measures of practitioner behaviour, but that they are more accurate than patient case notes (chart abstraction), which are often used as a measure of practitioner behaviour. Thus, despite understandable concerns of social desirability or acquiescence bias, changing responses towards vignettes may be considered a single, valid point along a causal pathway towards actual behaviour change.

We chose to use a vignette in the present study as we wanted to assess the practitioners' decisions about appropriate healthcare for a specific clinical scenario, which is precisely what clinical guidelines are intended to facilitate [6]. The vignette used was originally developed by Bombardier et al [105], and has since been used in several studies [10,106-108]. Some details of the vignette were anglicised and clarified prior to use, and further details regarding occupational duties and domestic responsibilities were added following comments received during the pilot study.

In light of key recommendations consistent across guidelines from many countries [16-19], and in a manner similar to the work of Rainville et al [109] with US physicians and Bishop and Foster [49] with UK physiotherapists, the primary questions relating to the vignette were designed to explore practitioner recommendations for patient behaviour in relation to (i) Work, (ii) Activity, and (iii) Bed-rest. Other secondary questions were added to explore investigations (including x-rays) and initial treatment interventions (e.g. advice, manual therapy, electrotherapy and exercise). The format chosen to capture responses to each of these primary questions was a 5-point Likert-type scale (Figure 3), based on questions originally used by Rainville et al [109].

**Figure 3 F3:**
[figure not shown]
**Questions and corresponding response options relating to a low back pain patient vignette **The points of dichotomisation for each scale, based on expert consensus, are shown (with arrows). For each scale, the response option(s) to the right of each arrow were interpreted as consistent with guideline recommendations. The numbers above and between response options represent the frequency of expert opinion for the point of dichotomy relating to that scale. Lenient interpretations (L) are placed on the top row above response options, and strict interpretations (S) on the bottom row. The five-point scales are considered ordinal. However, two items of the scale related to Work will be combined (highlighted in bold italics) to form a four-point scale in this case.

In order to inform the analysis of the results, and as the responses to these questions were being interpreted in light of guideline recommendations, an expert consensus exercise was performed. A group of 12 experts with extensive prior experience in LBP research were contacted independently and provided with a copy of the vignette and questions. Feedback from the experts confirmed that the five-point scales could be considered ordinal. However, it was recommended that two items of the scale related to Work should be combined (highlighted in bold italics in Figure 3) to form a four-point scale in this case.

There are two research questions relating to the primary outcome of reported behaviour. Each of these requires a different analysis to test for a statistically significant change between the two arms of the trial at the six-month post-intervention time-point. The two research questions are:

1. For each scale, can the intervention change the response proportions of 'guideline-consistent' and 'guideline-inconsistent' reported behaviour?

2. For each scale, can the intervention change the response proportions of reported behaviour across the entire range of responses?

The first of these questions represents the primary outcome measure for this study. It relates to changes in the proportions of responses either side of a predetermined cut-off point for each reported behaviour research question. Therefore, each of the original five-point scales will be dichotomised to create a new variable with categories defined as 'guideline-consistent' and 'guideline-inconsistent'. The location of the cut-off points for each scale is based on the expert consensus exercise. All experts were asked to give, where possible their 'lenient' and 'strict' interpretation of internationally agreed recommendations from primary care and occupational evidence-based guidelines [16-19] for each scale. These two interpretations will allow for a sensitivity analysis.

The wording and points of dichotomisation for each scale question are shown (with arrows) in Figure 3. For each scale, the response option(s) to the right of the arrow were interpreted as recommendations consistent with those of the guidelines. The positions of the red arrows indicate the location of cut-off points for the most frequent 'strict' expert interpretation of the guideline recommendations. The blue arrows indicate the location of cut-off points for the most frequent 'lenient' expert interpretation.

### Outcome measure 2: Practitioners' beliefs

Practitioners' beliefs regarding the relationship between back pain and physical function were measured using a modified version of the 13-item Health Care Providers Pain and Impairment Relationship Scale (HC-PAIRS) (Table 4), which was originally developed and validated by Rainville et al [110], and further studied by Houben et al [46]. The, responses for each item were collected with a 7-point Likert scale anchored from 'Completely disagree' (1) to 'Completely agree' (7). The scores are summed to form a total HC-PAIRS score, giving a theoretical range of possible scores from 13 to 91. Items 1, 6 and 12 were positively worded and were therefore reverse-scored for scoring and subsequent analysis. Factor analysis has shown the HC-PAIRS to measure a single factor of beliefs concerning the way in which LBP affects physical function [46]. Higher scores on the HC-PAIRS indicate a stronger belief that pain should affect daily function.

**Table 4 T4:** Modified items of the HC-PAIRS. Modified components are highlighted in bold.

**Item No.**	**Item**
1	**Low **back pain patients can still be expected to fulfil work and family responsibilities despite pain
2	An increase in pain is an indicator that a **low **back pain patient should stop what they are doing until the pain decreases
3	**Low **back pain patients cannot go about normal life activities when they are in pain
4	If their pain would go away, **low **back pain patients would be every bit as active as they used to be
5	**Low **back pain patients should have the same benefits as the handicapped* because of their **painful **problem
6	**Low **back pain patients owe it to themselves and those around them to perform their usual activities even when their pain is bad
7	Most people expect too much of **low **back pain patients, given their pain
8	**Low **back pain patients have to be careful not to do anything that might make their pain worse
9	As long as they are in pain, **low **back pain patients will never be able to live as well as they did before
10	**Low **back pain patients have to accept that they are disabled persons, due to their pain
11	There is no way that **low **back pain patients can return to do the things that they used to unless they first find a cure for their pain
12	Even though their pain is always there, **low **back pain patients often don't notice it at all when they are keeping themselves busy
13	All of **low **back pain patients' problems would be solved if their pain would go away

* The following caveat to item 5 was added as a footer in the modified version: We are aware that the term 'handicapped' is not liked by many people who have completed this questionnaire in the past but the research team are unfortunately unable to change this previously validated questionnaire as we may affect the results if we did so.

The original version of the HC-PAIRS was intended to assess health care providers' attitudes and beliefs about the degree to which chronic LBP justifies impairments and disability. It was published in 1995, and was itself adapted from a questionnaire developed for chronic pain patients, the Pain and Impairment Relationship Scale (PAIRS) that was first published in 1988 [111].

Modifications were made to the original HC-PAIRS in the present study for several reasons. Firstly, the evidence-based primary care [21] and occupational [22] guidelines, upon which the intervention package was based, were specifically developed for the management of *low *back pain rather than 'back pain' per se. Furthermore, the primary care guideline in particular is specifically based on the evidence for *acute *LBP and is clearly labelled as such. Moreover, the term 'chronic back pain patients' that Rainville et al [110] used to modify the PAIRS scale was based on the premise that the attitudes and beliefs measured would be valid only in chronic pain patients. Thus, the assumptions behind the design of these scales were representative of the knowledge at the time of publication. Certainly, one major development in LBP research since the late 1980's and early 1990's is that psychosocial factors have been shown to be involved much earlier in the course of LBP than was originally thought. Therefore, even though the PAIRS has not been formally tested in any other population than chronic pain patients [111-114], it is reasonable to argue that the practitioner beliefs measured by the modified version of the HC-PAIRS will be appropriate in the context of acute LBP patients.

### Sample size calculation

The primary outcome measure for this trial was the proportion of 'guideline-consistent' and 'guideline-inconsistent' reported behaviour, relating to the patient vignette for the key variables of work, activity, and bed-rest (Figure 3). This analysis is also in need of more statistical power than the alternative analysis using change in responses across the whole scale. It is therefore the appropriate criterion by which to estimate the target sample size for the trial. In light of previous studies on practitioner behaviour change [59,73], we defined a change of 10% in reported behaviour between the proportions of practitioners from baseline to the six-months post-intervention follow-up as a clinically meaningful change. Thisdifference is the same as the median effect size reported in a review of guideline implementation studies reported in a subsequent review [61,63].

There are no existing data on 'guideline consistent' responses on which we could base our sample size calculation. To show a 10% difference in the proportion of these practitioners who, at the six-month post-intervention follow up, would give 'guideline consistent' responses to this questionnaire, the greatest statistical power is needed when proportions in each group are 45% and 55%. To show this difference at the 5% significance level with 90% power, valid data from at least 543 participants in each arm of the trial are needed for analysis (1086 total). Previous studies using a similar questionnaire format to measure outcomes have shown a response rate of between 31% and 65% [10,41,73,109,115]. Based on these figures, and the overall response rate of the pilot study, a recruitment rate of approximately 50% was anticipated at baseline. Allowing for 40% loss to follow-up, 900 practitioners had to be recruited into each arm of the trial at baseline (1800 total). Further allowing for the estimated recruitment rate of 50% at baseline, approximately 3600 practitioners needed to be invited to participate at the start of the study. A total of 3604 were actually invited. Such over-sampling strategies are typical of studies on healthcare practitioners based on survey methodology [e.g. [41,115]].

### Data handling and analyses

The anonymised questionnaire data have been transferred into electronic format using a pre-coded datafile via Statistical Package for Social Scientists (SPSS) Data Entry (version 3.0) software, which is designed to reduce systematic errors during data entry. Data were independently entered by an experienced data entry administrator, who was blind to the participant identities. For purposes of reducing error, 20% of all data entered in the SPSS datafile was checked by one of the research team, blind to participant intervention allocation at the time.

As this is a pragmatic trial, the primary analysis will be performed on an intention to treat basis, as recommended by Bland [71]. It will include all participants randomised, even if they did not subsequently receive or read the intervention package when allocated. A proposed secondary analysis will focus on participants who appear to have read the information package, as identified by means of responses to a question on the follow-up questionnaire acting as a proxy. Data will be analysed using SPSS (version 11.5). All significance tests will be two-sided and statistical significance will be set at the 5% level.

The reported behaviour outcomes require a different analysis for each of the two research questions. The dichotomous variable, with categories defined as either 'guideline-consistent' or 'guidelineinconsistent', will be analysed using a binomial regression model (primary analysis). This will allow for between-arm differences of the proportions of responses that fall within each category at follow-up to be tested. The points of dichotomy will be based on the 'lenient interpretation' for each variable, as per the expert consensus exercise (Figure 3). The 'strict interpretation' for each variable will be used to provide sensitivity analyses. The original ordinal data will be analysed using an ordinal regression model, in which between-arm differences of proportions across all follow-up reported behaviour data may be tested. Baseline reported behaviour responses will be included in each model as a covariate. The secondary clinical and demographic data collected at baseline will be inspected and will also be included as covariates in the analyses, depending on the proportions of variance shared between these variables.

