### Randomisation and intervention allocation

The baseline questionnaire was completed prior to subsequent intervention allocation (Figure 1). Practitioners that responded to the baseline questionnaire and consented to take part further in the study became the study 'participants'. A member of the research team, based in another institution and who was not involved in the data collection, produced a blind, random allocation of each participant to either control or intervention arms, using only a list of participant's anonymous unique study numbers in StatsDirect software package. The intervention packages were posted with a brief covering letter to those allocated to the intervention arm in March 2004.

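### The proposed analysis of practitioners who appear to have read the package selects on a post-randomisation response, so a plain subset comparison can show an effect when none exists

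*Protocol article*

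**What the plan says.** In the protocol article, Data handling and analyses makes intention to treat the primary analysis: "It will include all participants randomised, even if they did not subsequently receive or read the intervention package when allocated". It then adds: "A proposed secondary analysis will focus on participants who appear to have read the information package". The means of finding these readers comes at six months, not before allocation: "as identified by means of responses to a question on the follow-up questionnaire acting as a proxy". The same paragraph sets one general testing rule: "All significance tests will be two-sided and statistical significance will be set at the 5% level".

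Two other sections show who had a package to read. Randomisation and intervention allocation says: "The intervention packages were posted with a brief covering letter to those allocated to the intervention arm in March 2004". Control arm says that controls "were sent no further information prior to the six-months post-intervention follow-up questionnaire".

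For the reader analysis the article names no comparator and no estimator, and it does not label the result as non-randomised. It does plan to put baseline reported behaviour into each model, and to add other baseline clinical and demographic variables depending on the variance they share.

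**The concern.** Reading is something a participant does, or says they did, after allocation. It is recorded at six months on the same form as the vignette answers. Practitioners who open, read and remember a guideline package may already lean towards its advice, and those who wish to give the approved answer may both claim to have read it and answer the vignette accordingly. The article gives grounds to expect this. The Background links divergence from guidelines to practitioners' beliefs, and the section on reported behaviour accepts that social desirability and acquiescence are understandable concerns with vignettes.

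A reader-only result would naturally be taken as the effect of the package when it is actually read. If readers differ from other practitioners for reasons that precede the package, part or all of the difference is selection. The article expects a small effect per practitioner and treats 10 points as meaningful, so a false difference of a few points would matter.

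**Working it through.** **Inputs from the article.** Two-sided 5% level; 90% power; 45% against 55%; 543 analysed per arm (Sample size calculation). Package sent to the intervention arm only. Readers identified at follow-up.

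**Inputs not in the article.** The reading rate r and the gap D in guideline-consistent responding between intervention-arm readers and non-readers. Both are assumptions, shown as ranges.

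**Step 1: the plan's own figure.** Without continuity correction, n = [1.960 x sqrt(2 x 0.5 x 0.5) + 1.282 x sqrt(0.45 x 0.55 + 0.55 x 0.45)]² / 0.10² = (1.386 + 0.902)² / 0.01 = 523.3, or 524. With continuity correction, n = (523.3/4) x [1 + sqrt(1 + 4/(523.3 x 0.10))]² = 543.1. The stated 543 is reproduced and is not in dispute.

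**Step 2: the false difference.** Suppose the package does nothing and 50% are guideline-consistent in both arms. In the intervention arm r x pR + (1 - r) x pN = 0.50 and pR - pN = D, so pR = 0.50 + (1 - r) x D. Controls stand at 0.50. Readers against all controls therefore differ by (1 - r) x D with no effect present.

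**Step 3: the false-positive rate.** Unadjusted two-proportion test, 543r readers against 543 controls. Worked case, r = 0.5 and D = 0.10:
- pR = 0.55, with 271.5 readers; pooled proportion 0.5167.
- Null standard error = sqrt(0.5167 x 0.4833 x (1/271.5 + 1/543)) = 0.0371, so the critical difference is 1.96 x 0.0371 = 0.0728.
- Actual standard error = sqrt(0.55 x 0.45/271.5 + 0.25/543) = 0.0370.
- Rejection probability = Phi((0.050 - 0.0728)/0.0370) plus a negligible lower tail = 27%.

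The same calculation over the range (false difference in points, false-positive rate in brackets):

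| Reading rate | Gap 5 | Gap 10 | Gap 20 |
|---|---|---|---|
| 30% | 3.5 (12%) | 7 (35%) | 14 (89%) |
| 50% | 2.5 (10%) | 5 (27%) | 10 (77%) |
| 70% | 1.5 (7%) | 3 (15%) | 6 (44%) |
| 90% | 0.5 (5%) | 1 (6%) | 2 (10%) |

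With D = 0 the rate is 5%. Comparing the arms as randomised gives 5% throughout.

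**Step 4: other comparators.** Readers against non-readers within the intervention arm shows the whole gap as a false effect: at 50% reading and a 10-point gap, 65% false positives. If the proxy question is put to both arms and positive answers are compared, the item tracks reading only in so far as allocation changes the answers. Once it does, the two subsets are selected in different ways.

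**Step 5: baseline adjustment.** In a simulation under no effect (1,000 runs, 543 per arm, about half reading, reading related to underlying guideline orientation), adjusting for one binary baseline response lowered the false-positive rate from 39% to 25% under moderate selection and from 86% to 63% under strong selection. The adjusted false effects were 4.5 and 8.3 points. The arms as randomised gave 3.4% to 6.5%. This illustrates incomplete removal; it does not forecast this trial, because the article allows a fuller adjustment.

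**The case against.** The strongest reply is that the criticised comparison is not in the document. The article says only that the analysis will focus on apparent readers. It is a condensed account, and the estimator for a proposed secondary analysis may sit in a statistical analysis plan that is not shown. A complier-average analysis could also be said to focus on readers. This stands in part, and several stronger readings must be set aside:

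- A reader might infer that the plan specifies readers against all controls. It does not. That comparator is used above because it is the simplest case.
- A reader might infer that the question is asked in one arm only. The article does not show its wording or who answers it. What is documented is that only one arm was sent the package.
- A reader might infer that adjustment rests on a single vignette item. The article plans baseline behaviour responses, in the plural, and possibly further baseline variables. Beliefs, self-confidence and attitudes to research are all measured at baseline (Table 3), though the text does not say whether they would be included. Fuller adjustment could reduce the bias by more than Step 5 shows, but nothing guarantees that it captures why people read the package.
- A reader might take one cell of the table as the expected bias. The documents support no particular cell, and at 90% reading the problem is small.

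What survives is that the article commits to a population defined by a post-randomisation response, and none of the plain subset comparisons examined above restores the randomised comparison.

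**Conclusion.** The point holds as a moderate one about a secondary analysis. That a reader subset can produce an effect under the null follows from the design. The size does not, because it depends on the reading rate, the gap and the adjustment, none of which the documents settle. A bias in favour of the package is plausible if readers are the more guideline-minded practitioners, but that is also an assumption. The bias vanishes if reading is unrelated to the outcome and is minor if nearly everyone reads the package. It would be wrong to infer that the trial's main conclusion is at risk, since the intention-to-treat analysis does not use reading status.

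**What to change.** Replace the reader subset analysis with a complier-average causal effect: randomised arm as instrument, reported reading as exposure (set to 0 in controls, who were not sent the package), and the same baseline covariates as the primary model. Without covariates this is the intention-to-treat difference divided by the proportion of the intervention arm who report reading, so it stays centred on zero when the package has no effect.

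State the assumptions with it:
- Allocation acts only through reading. The package contains a poster and single-sheet recommendations (Table 2) that might act without being reported as read.
- Controls had no access to the package.
- Under-reported reading inflates a non-null estimate. For example, if 70% read but only 50% say so, an intention-to-treat difference of 10 points gives 10/0.5 = 20 instead of 10/0.7 = 14.3.
- Exposure is seen only in follow-up responders, and the plan allows for 40% loss.

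Report reader-only figures as descriptive and non-randomised, without a test. The change is to analysis wording and uses a question already on the follow-up form. The cost is a wider interval than the subset comparison would give.
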